### Procedure for unblinding if needed {17b}

Not applicable.

## Data collection and management

### Plans for assessment and collection of outcomes {18a}

#### Training of assessors

Before the start of enrolment, all study personnel involved in testing (PTs, nurses, research nurses) or delivery of the intervention (PTs) received training in all methods to be used in the study from ER, JD, and MA. Written instructions and checklists for the flow of participants through the study were developed and delivered to study personnel in printed documents and digital forms. A digital communication platform between involved personnel was established using Microsoft Teams (MS-Teams) (Microsoft Corporation, [name]). Access to specific MS-Teams areas (and associated files) was restricted and based on a need-to-know basis. All data collection instruments were provided with written instructions and video recordings or slide shows with instructions for specific methods such as the IMT-training device. During the training of physiotherapists before the first inclusion, workshops were held (digitally) where all protocols, tests, questionnaires, and related procedures were discussed. Between workshops, physiotherapists also completed a task where data for a hypothetical participant was to be registered into the protocols according to the procedures in the study. The assignment was discussed in groups at the follow-up workshop, and any questions or unclarity regarding the protocols or procedures were discussed and resolved. The digital platform is available through the study course to both promote learning of procedures at the beginning of the study and prevent procedural drift over time.

### Plans to promote participant retention and complete follow-up {18b}

An intention-to-treat approach will be used. Thus, all randomised participants will be considered to have received the treatment to which they were allocated, even if they choose to discontinue their participation or have low compliance with the treatment. Outcome data available from medical records (post-operative complications) will be collected as planned unless participants do not explicitly state that this should not be done.

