### Eligibility criteria {10}

Inclusion criteria (for participants):Awaiting surgery due to suspicion of colorectal cancer or colorectal liver metastasesAge 65 years or olderMaximal walking speed below 2 m/sResidential address in Stockholm CountyUnderstand and speak the Swedish language

Exclusion criteriaSurgical procedures which hinder post-operative measurements (for instance, hyperthermic intraperitoneal chemotherapy, abdominoperineal rectal resection with musculocutaneous flap)If time to surgery < 14 days and postponing the operation for additional 7–14 days constitutes a medical risk (as assessed by the patient’s clinicians)

Inclusion criteria (*for sites)*Organisational readiness for participation (availability of vital staff: PTs, nurses, doctors)

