#### Criteria for discontinuing or modifying allocated interventions {11b}

Adverse events (AE) are monitored throughout the intervention period. Should AEs occur, the intervention is stopped, and the surgeon responsible for the subject’s cancer care is contacted and decides whether the interventions should be discontinued or proceed as planned. Should participants choose to withdraw consent or discontinue for an AE, they will be retained in the study, and an intention-to-treat approach will be used in the analysis.

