#### Primary outcomes

Pre-operative outcome: change in maximal walking distance

Difference between treatment groups regarding the change in walking distance during a 6-min walk test (6MWT) [34] during the pre-operative period. The outcome is the maximal walking distance (metres) participants can cover in 6 min. Comparisons between changes in distance between the intervention and control groups will be performed. A difference of 50 m will be considered clinically significant and was used in the power calculations for sample size.

Time points: Baseline (*t*_0_), at hospital admission (or the day before (*t*_1_), and at discharge from hospital (*t*_3_).

Post-operative outcome: complications 30 days post-surgery

The difference in complications between groups regarding post-operative complications (PC) 30 days post-surgery according to Clavien-Dindo (CD) and any complications up to day 30 will be considered [35]. The CD grading system allows for quantifying post-operative complications based on the type of treatment needed to correct the complication. Grade I requires the least treatment; grade V is death. The number and proportion of participants with PC will be presented. No minimal important difference (MID) level for the CD system is recommended, and in the present study, a difference of 1 grade is considered important and was used in the power calculations for sample size.

Time-point: 30 days post-surgery (*t*_4_)

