### Implementation {16c}

MA generated the random allocation table using free software available online (http://www.jerrydallal.com/random/random_block_size.htm). Enrolment of participants is conducted by site-personal (nurses or PTs) whom first approach potential participants identified from a list of patients referred to the hospital for diagnosis and possible surgical treatment. If potential participants match the inclusion criteria, informed consent is obtained by study personnel (nurses or PTs) prior to baseline testing. After the first baseline visit (*t*_0_), participants are randomised and allocated using the randomisation function of the electronic database of the study that ensures the concealment of the allocation order. Randomisation is performed by ER, MA, JD, or ST).

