### Methods in analysis to handle protocol non-adherence and any statistical methods to handle missing data {20c}

All participants will be analysed within the group to which they are randomised. Missing data will be handled by imputation, with the exact method depending on the type of missingness [52].

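### A double negative reverses the rule for collecting complication data from medical records, and the discontinuation section keeps participants who withdraw consent without the opt-out that rule evidently intends

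*Protocol article*

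**What the plan says.** Three sections of the protocol article bear on participants who leave the intervention or the study.

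- **Retention, {18b}.** Under intention to treat, "all randomised participants will be considered to have received the treatment to which they were allocated", including people who discontinue participation or comply poorly. The next sentence covers outcome data available from medical records, naming post-operative complications: these are to be collected as planned "unless participants do not explicitly state that this should not be done".
- **Discontinuation, {11b}.** "Should participants choose to withdraw consent or discontinue for an AE, they will be retained in the study", with an intention-to-treat analysis. Withdrawing consent and stopping for an adverse event are treated alike, and no right to refuse further collection is mentioned.
- **Missing data, {20c}.** Everyone is analysed in the group to which they were randomised. "Missing data will be handled by imputation, with the exact method depending on the type of missingness".

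The data concerned are those of the second primary outcome, complications to day 30 by Clavien-Dindo grade (Primary outcomes), to be analysed by ordinal logistic regression ({20a}).

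**The concern.** The {18b} sentence tells site staff whether to extract the second primary outcome from the notes of someone who has left the study. Followed as written, it would discard obtainable outcomes from people who never objected and collect them from people who did. The first defeats the intention-to-treat aim stated just before it; the second overrides a refusal.

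Section {11b} adds a separate difficulty. It puts two different events under one rule: ending the exercise, which says nothing about data use, and withdrawing consent, which may. Four recruiting hospitals have to apply these rules consistently.

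The loss need not be balanced between arms. The stop-on-adverse-event rule in {11b} concerns the exercise intervention, so discontinuation for that reason would arise mainly in the exercise arm. If outcomes were dropped for people who leave silently, the complications comparison could be affected unevenly.

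**Working it through.** The plan states no figure for this point, so the check is one of logic, followed by a note on scale.

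**Step 1: the {18b} rule taken literally.** The form is: collect, unless X. Here X is "unless participants do not explicitly state that this should not be done", that is, the participant has *not* objected.

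| Participant who discontinues | Is X true? | {18b} as written | {18b} as evidently meant | {11b} as written |
|---|---|---|---|---|
| Says nothing about records | Yes | Not collected | Collected | Retained |
| Explicitly objects | No | Collected | Not collected | Retained |

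The third and fourth columns are opposite in both rows, so the rule is fully reversed.

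**Step 2: {18b} against {11b}.**

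- *{18b} as written:* the first row conflicts, because {11b} retains the silent leaver and {18b} drops that person's complication data.
- *{18b} as meant:* the first row agrees. The second does not, because {18b} allows refusal of record collection while {11b} retains a person who withdraws consent with no exception.

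Correcting {18b} alone therefore leaves one disagreement.

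**Step 3: what this means for power.** Inputs from the Clavien-Dindo power section: difference 1 grade, SD 1.32, alpha 5% (taken as two-sided), power 0.80, correction factor 0.864.

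- Normal approximation per arm: 2 × (1.960 + 0.842)² × (1.32/1)² = 2 × 7.85 × 1.742 = 27.4, rounded up to 28.
- t-test per arm: 28.34, rounded up to 29, so 58 in total, as stated.
- 58 / 0.864 = 67.1, stated as 67.

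The plan's figures reproduce. With 160 randomised, the margin over the stated requirement is 160 − 67 = 93 participants. Even at an assumed 20% loss (128 left), t-test power on the plan's own assumptions, with the group size multiplied by 0.864, is 97.7%. Power for this outcome is therefore not what is at stake; selective loss and respect for refusals are.

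**Step 4: effect on the estimate.** This would need the number of people who discontinue, the split by arm, how many object, and their complication grades. The documents give none of these, so no size is computed.

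**The case against.** The strongest reply is that nobody would follow the sentence as written. Its opening words and the intention-to-treat sentence before it make the purpose plain: collect unless the person objects. Section {27} also places personal data under the GDPR. Retained in {11b} may mean only kept in the analysis set, with {18b} supplying the more specific rule on records. The article also condenses a fuller protocol, which may be worded correctly.

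Much of this stands. It makes actual mishandling unlikely, and shows that the sections can be aligned. It does not make the sentence right: this is a rule stated wrongly, not a detail left out, and {11b} does not say that retained has the narrower meaning.

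A reader might infer something stronger: that the imputation rule in {20c} would invent complications for people never operated on, or questionnaire scores for people who have died. The starting facts are fair. Eligibility is "Awaiting surgery due to suspicion of colorectal cancer" or colorectal liver metastases, and "participants are randomised and allocated using the randomisation function of the electronic database" after the baseline visit and before the operation, so a randomised participant without surgery is possible. The documents still do not support the inference:

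- {20c} imputes missing data and leaves the method open. A grade after an operation that never took place is undefined, not missing, and nothing in {20c} says to impute it. An analysis plan that is not shown may settle this.
- Nothing in {20c} is reversed; the reversal is confined to {18b}.
- Death is already a category of the second primary outcome: "Grade I requires the least treatment; grade V is death". Death from complications scores 100 on the Comprehensive Complication Index, and mortality is collected separately.
- The first primary outcome is change in walking distance in the pre-operative period, which a post-operative death does not touch.

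A further inference, that complications should be analysed mainly in operated participants, is not supported either. It would condition on an event after randomisation and depart from the stated intention-to-treat approach.

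**Conclusion.** The point holds for two statements: the record-collection rule in {18b} is reversed, and {11b} does not agree with the opt-out that {18b} evidently intends. Both can be seen in the text and need no assumption about an unseen analysis plan. They should be corrected because they govern how a primary outcome is obtained and what happens when someone refuses.

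The size cannot be stated. The claim that the comparison could be affected assumes that some participants discontinue and that staff apply the sentence literally; the claim of imbalance further assumes that more of them leave the exercise arm. The documents establish none of these. No loss of validity is shown, and the stated sample sizes are not in dispute.

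The documents do not say how participants without surgery are handled, nor how death enters the discharge walk, length of stay or the 6- and 12-month questionnaires. That is at most a request for clarification.

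**What to change.** - **{18b}:** remove the surplus negation, so that record-based complication data are collected for every randomised participant, including those who stop early, except where the person has expressly refused.
- **{11b}:** separate two events. A participant who only stops the exercise is retained, followed up and analysed as randomised. For a participant who withdraws consent to further data collection, data gathered up to that point stay in the analysis as permitted, and nothing further that the person refuses is collected.
- **Analysis plan (clarification only):** state that outcomes that do not exist are not treated as missing data for imputation. No main-analysis population is prescribed here.

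The cost is two reworded passages and one clarifying sentence, with no new data, visits or sample size. Section {25} sends relevant changes to the ethical review board before implementation, so a short amendment may be needed. As recruitment began in March 2021, the sponsor should also confirm which reading the sites have applied to participants who have already discontinued.

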### Data management {19}

Data collected in written protocols or checklists will be stored in a secure place (locked file storage or equivalent) and later transferred into an electronic data storage using REDCap electronic data capture tools hosted at Karolinska Institute [50, 51]. REDCap is a secure, web-based software platform designed to support data capture for research studies, providing (1) an intuitive interface for validated data capture; (2) audit trails for tracking data manipulation and export procedures; (3) automated export procedures for seamless data downloads to common statistical packages; and (4) procedures for data integration and interoperability with external sources.

### Confidentiality {27}

All personal data collected will be handled according to EU data protection rules described in the General Data Protection Regulation (GDPR).

### Plans for collection, laboratory evaluation, and storage of biological specimens for genetic or molecular analysis in this trial/future use {33}

Not applicable.

## Statistical methods

### Statistical methods for primary and secondary outcomes {20a}

An intention-to-treat approach will be used and supplemented with a per-protocol analysis. Primary and secondary outcomes will be compared between groups. Data will be examined regarding normality, missing data, and outliers.

The hypothesis is that prehabilitation will result in better physical function in the pre-operative phase and fewer complications in the post-operative phase. This will be tested against the null hypothesis, i.e. prehabilitation will result in similar walking distance and complications as in the usual care group. An analysis of covariance (ANCOVA) will be performed to assess change in pre-operative physical function between groups (first primary outcome). Ordinal logistic regression will be used to analyse the differences between groups in post-operative complications (second primary outcome).

Demographics for the study population will be presented using descriptive statistics (mean and SD, median with IQR or min-max, and numbers with proportions) depending on the type of data collected and its distribution. Adherence to supervised exercise sessions will be presented using descriptive statistics (percentage of attended out of planned supervised sessions). Furthermore, all primary and secondary outcomes will be presented using these descriptive statistics at all time points. Differences between groups at single time points will be analysed by unpaired *t*-test, Mann-Whitney-test, chi-squared-test, or Fisher’s exact test, depending on the data type and distribution. General linear mixed models (GLMM) will be used to assess differences between groups over several repeated measurements, adjusting for relevant covariates. Point estimates and test statistics will be reported with the two-sided *p*-value and complemented with 95% confidence intervals to describe the direction and magnitude of the effect.

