**Methods:**

Participants will be included from four sites in Stockholm, Sweden. A total of 160 participants will be randomly assigned to intervention or control conditions. Simple randomisation (permuted block randomisation) is applied with a 1:1 allocation ratio. The intervention group will perform home-based exercises (inspiratory muscle training, aerobic exercises, and strength exercises) supervised by a physiotherapist (PT) for a minimum of 6 sessions in the pre-operative period, complemented with unsupervised exercise sessions in between PT visits. The control group will receive usual care with the addition of advice on health-enhancing physical activity. The physical activity behaviour in both groups will be monitored using an activity monitor. The primary outcomes are (1) change in physical performance (6-min walking distance) in the pre-operative period and (2) post-operative complications 30 days after surgery (based on Clavien-Dindo surgical score).

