**Discussion:**

If patients achieve functional benefits by exercise in the short period before surgery, this supports the implementation of exercise training as a clinical routine. If such benefits translate into lower complication rates and better post-operative recovery or health-related quality of life is not known but would further strengthen the case for pre-operative optimisation in colorectal cancer.

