### Secondary objectives

To compare the groups regarding the following aspects:Change in physical function (lower extremity functional strength, inspiratory muscle strength, walking distance) at the end of the pre-operative period and at dischargeLength of stay and destination of dischargeSelf-reported symptoms (patient-reported recovery) at dischargeLong-term effects (6 months and 1 year post-surgery) on health-related quality of life, physical activity, activities of daily living, and patient-reported recovery.

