#### Power calculation for 6MWT

For the 6MWT, an SD of 111.5 m was assumed based on a previous study. A clinically important difference of 50 m was used in the calculations. To be able to detect a difference of 50 m, with an alpha level of 5% and a power of 0.80, a total sample size of 160 participants would be needed.

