#### Power calculation for CD-classification

For the outcome of post-operative complications, an SD of 1.32 was assumed for the CD scale. A “pitman efficiency factor” was applied by dividing the estimated sample size by 0.864 to adjust for the CD classification as an ordinal scale. We assumed a difference of 1 grade between groups to be of clinical importance. With an alpha level of 5% and a power of 0.80, a total sample size of 58 would be needed. With the application of the correction factor (dividing the total sample size by 0.864), the final sample size needed is 67 evaluable participants.

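### Two primary outcomes are each planned at a full two-sided 5% with no rule for combining them; if either can support a primary claim, the familywise error is up to 9.75%

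*Protocol article*

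**What the plan says.** The Abstract (Methods) names the first of two primary outcomes: "The primary outcomes are (1) change in physical performance (6-min walking distance) in the pre-operative period". The second is post-operative complications at 30 days on the Clavien-Dindo scale.

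The section on statistical methods for primary and secondary outcomes {20a} gives each outcome its own analysis. The first is an ANCOVA of pre-operative change. For the other, "Ordinal logistic regression will be used to analyse the differences between groups in post-operative complications (second primary outcome"). The null is worded for both outcomes together: "This will be tested against the null hypothesis, i.e. prehabilitation will result in similar walking distance and complications as in the usual care group".

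The power calculation for 6MWT is done "with an alpha level of 5% and a power of 0.80". The one for Clavien-Dindo repeats it: "With an alpha level of 5% and a power of 0.80". The article gives no split of alpha, no test order and no statement that both outcomes must be met.

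On how results will be used, the Abstract (Discussion) says: "If patients achieve functional benefits by exercise in the short period before surgery, this supports the implementation of exercise training as a clinical routine". Fewer complications are described there as strengthening the case further.

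On time points, Primary outcomes lists baseline and admission for the walk test, "and at discharge from hospital" as well. Secondary objectives includes "Change in physical function (lower extremity functional strength, inspiratory muscle strength, walking distance) at the end of the pre-operative period", and also at discharge.

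**The concern.** With two primary outcomes, the error rate of the trial's main claim depends on the rule that joins them. Requiring both holds the error at or below 5% without adjustment. Letting either one carry the claim at 5% does not. The article does not say which applies, and its one statement on interpretation lets a walking gain stand alone. Without a fixed rule, the trial could present whichever primary outcome falls below 0.05, and the claim would rest on a weaker standard than 5%.

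The choice also bears on the sample size. N = 160 is what 6MWT needs at a full 5%, so some later choices of rule would leave that outcome short of its planned power.

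The double listing of walking distance is a smaller problem of the same kind: it leaves open which walking comparison is the primary one.

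**Working it through.** **Inputs.** All are from the sample size and power sections and {20a}: 6MWT difference 50 m, SD 111.5 m; Clavien-Dindo difference 1 grade, SD 1.32, efficiency factor 0.864; independent t-test, equal groups, 5% alpha, power 0.80; two-sided p-values.

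**Reproducing the plan's figures** (two-sample t-test, noncentral t)
- 6MWT: d = 50/111.5 = 0.448. This needs 79.04, so 80 per arm, total 160. Matches.
- Clavien-Dindo: d = 1/1.32 = 0.758. This needs 28.34, so 29 per arm, total 58. Then 58/0.864 = 67.1, stated as 67. Matches.
- A one-sided 5% test would need only 124 for 6MWT (normal approximation), so the stated 160 uses a two-sided 5%, with nothing held back for the second outcome.

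**Familywise error if either outcome can carry the claim**
- Independent tests: 1 − (1 − 0.05)² = 1 − 0.9025 = 9.75%.
- Correlated normal test statistics: 9.64% at r = 0.2, 9.07% at r = 0.5, 7.04% at r = 0.9.

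So 9.75% is the upper figure, and moderate correlation lowers it little.

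**If both are required:** the error is at most 5%.

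**What each rule costs at N = 160.** Single-test power for 6MWT is 80.5% at 5% and 71.6% at 2.5%. For Clavien-Dindo, with 80 × 0.864 = 69.12 effective per arm, it is 99.3% at 5% and 98.5% at 2.5%.

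| Rule | 6MWT power | Note |
|---|---|---|
| Fixed sequence, 6MWT first | 80.5% | Clavien-Dindo is confirmatory only after 6MWT succeeds |
| Both required | 80.5% for its own test | Joint power 0.805 × 0.993 = 79.9% |
| Holm | 80.3% | 0.7164 + 0.9850 × (0.8048 − 0.7164) = 0.8035 |
| Plain 2.5% split | 71.6% | 192 participants would restore 80% |

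The joint-power and Holm figures assume independent tests. The Holm figure also assumes the planned 1-grade effect on complications. With no effect there, Holm gives 0.7164 + 0.025 × 0.0884 = 71.9%, little better than the plain split.

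**Time points side by side.** Primary outcomes heads the walk test as a pre-operative outcome and defines it as change over the pre-operative period, yet lists discharge among its time points. Section {20a} analyses pre-operative change as the first primary outcome. Secondary objectives lists walking distance at the end of the pre-operative period and at discharge. As written, each of the two follow-up walks is therefore listed as both primary and secondary.

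**The case against.** The strongest reply is that the article never says either outcome is enough. The objectives expect benefit in both the short and the longer view, the sample size section states one primary hypothesis in two parts, and {20a} joins better function and fewer complications with an and. Read that way, both must succeed and the error is at most 5%. This stands as far as it goes: an either-wins rule is something a reader might infer, not something the document states. The Abstract's remark is interpretation rather than a decision rule. It lets a walking gain stand alone but does not say that fewer complications alone would count, and it fits a walking-first order at least as well. What it does not fit easily is a requirement that both succeed.

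It can also be said that the null-hypothesis sentence is informal and that no global test is described. That is fair; the point rests on two separate 5% tests with no joining rule, not on that sentence alone.

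A separate analysis plan may set the rule, and a fixed sequence or a both-required rule would fit N = 160 unchanged. That lowers the severity. It does not settle the point, because the article already fixes 5% for each outcome and a plain split chosen later would underpower 6MWT.

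The 9.75% counts two-sided rejections in either direction. Counting only false findings of benefit, the figures are 1 − 0.975² = 4.94% against 2.5% for one test. The relative increase is much the same.

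A reader might also count discharge walking distance as a third primary test and quote a larger error. The documents do not support that: the primary walking outcome is defined and analysed as pre-operative change, and discharge comes after surgery. Its listing there is an inconsistency to reconcile.

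**Conclusion.** The point holds as a gap in the stated testing rule and should be fixed. Two primary outcomes are tested separately, each at a full two-sided 5%, and nothing says how they combine. If either can support a primary claim, the familywise two-sided error is up to 9.75%, or about 9.1% at correlation 0.5. If both are required, it is at most 5%. The first figure is conditional on a rule that the article makes plausible but does not state.

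It would go too far to say that the trial doubles its declared error rate. The document declares no familywise rate; its 5% is the alpha of each separate power calculation.

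The mixed status of the walking time points is a contradiction in the text and holds without any assumption.

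**What to change.** State one rule in {20a} before any outcome data are compared by arm. The simplest follows the article's own numbering: test the baseline-to-admission change in 6MWT at two-sided 5%, then 30-day Clavien-Dindo at two-sided 5% only if the first is significant. This holds 5% at N = 160 and leaves 6MWT power as planned. Its cost is that the complications result is descriptive if 6MWT is not significant, although that outcome has the higher planned power.

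Holm is an acceptable alternative if the sponsor wants complications to be able to succeed alone; its 6MWT power depends on the planned complications effect being real. Requiring both outcomes is also valid, provided the Abstract's statement on implementation is brought into line. A plain 2.5% split is not advisable at this sample size.

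Separately, reconcile Primary outcomes, Secondary objectives and {20a} so that each walking comparison has one status: baseline-to-admission change primary only, discharge secondary only.

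The whole change is about a paragraph of text and needs no further participants.

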## Methods: participants, interventions, and outcomes

### Study setting {9}

Screening and recruitment of participants are performed at four sites: Karolinska University Hospital in Solna and Huddinge, South General Hospital, and Ersta Hospital, situated in the Stockholm city area, Sweden.

Physiotherapists (PT) from the Stockholm County home-rehabilitation units will deliver the intervention in the participants’ homes. Fifteen home-rehabilitation units have been recruited to participate in the study, chosen for maximal coverage based on geographical dispersion and for operational purposes limited to the Stockholm County area.

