### Methods for additional analyses (e.g. subgroup analyses) {20b}

Sub-group analyses based on surgical procedure (open or minimally invasive) are planned.

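### The ordinal model for complications is stated without covariates, which costs some power at effects below one grade, and no decisive analysis is named for secondary outcomes with a baseline

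*Protocol article*

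**What the plan says.** The section on statistical methods {20a} gives one sentence to each model:

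- 6-minute walk (6MWT): "An analysis of covariance (ANCOVA) will be performed to assess change in pre-operative physical function between groups (first primary outcome").
- Complications: "Ordinal logistic regression will be used to analyse the differences between groups in post-operative complications (second primary outcome"). No covariate is named.
- Repeated outcomes: "General linear mixed models (GLMM) will be used to assess differences between groups over several repeated measurements, adjusting for relevant covariates".
- Other comparisons: "Differences between groups at single time points will be analysed by unpaired" t-test, Mann-Whitney, chi-squared or Fisher's exact test, chosen by data type and distribution. The preceding sentence has all primary and secondary outcomes described at every time point.

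On design, the abstract says "Simple randomisation (permuted block randomisation) is applied with a 1:1 allocation ratio", and the sequence generation section gives varying block sizes of 2, 4 or 6. Neither mentions a stratification factor. Under study setting, "Screening and recruitment of participants are performed at four sites". The eligibility criteria admit surgery for suspected colorectal cancer and for colorectal liver metastases. The only stated analytic use of a surgical factor is for subgroups: "Sub-group analyses based on surgical procedure (open or minimally invasive) are planned".

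The Charlson index and the 6MWT are both measured at baseline, before randomisation.

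**The concern.** Adjustment is written in for the mixed models but not for the ordinal regression, which carries a primary outcome. Site and indication could plausibly affect complications, yet as described neither the allocation nor the model accounts for them. Leaving prognostic variables out of a logistic-type model pulls the estimated effect towards the null and lowers power. The data needed to avoid this are already collected.

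Chair stands, inspiratory pressure, the EORTC scales, the ADL-staircase and the Physical Activity Scale for the Elderly (PASE) each have a baseline value and later measurements. As worded, each could be analysed by an unpaired test at a time point and also by the adjusted mixed model. The two can disagree, and the article does not say which one counts.

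**Working it through.** **1. The plan's own figures.** For a two-sided 5% test with 80% power, n per arm = 2(1.96 + 0.842)² × SD²/δ².

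- 6MWT (SD 111.5 m, δ 50 m): 79 by the normal formula. The exact t-test gives 79.04, rounded up to 80 per arm, or 160 in total.
- Clavien-Dindo (SD 1.32, δ 1 grade): 28 by the normal formula. The exact t-test gives 28.34, rounded up to 29 per arm, or 58 in total. Then 58/0.864 = 67.1.

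The stated 160, 58 and 67 are all reproduced.

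**2. Unadjusted power for complications at N = 160.** The effective size per arm is 80 × 0.864 = 69.12. SE = 1.32 × √(2/69.12) = 0.2245. Power = Φ(δ/SE − 1.96).

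- δ = 1: 1/0.2245 − 1.96 = 2.49, so power is 99.4%.
- The difference detectable with 80% power is 2.80 × 0.2245 = 0.63 grade.

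**3. Effect of adjustment, linear approximation.** The SE is multiplied by √(1 − R²). R² is an assumption; the article gives none.

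| δ (grades) | Unadjusted | R² 0.05 | R² 0.10 | R² 0.20 | R² 0.30 |
|---|---|---|---|---|---|
| 0.4 | 42.9% | 44.7% | 46.7% | 51.3% | 56.7% |
| 0.5 | 60.5% | 62.7% | 65.1% | 70.2% | 75.9% |
| 0.6 | 76.2% | 78.3% | 80.4% | 84.8% | 89.1% |
| 1.0 | 99.4% | 99.5% | 99.7% | 99.9% | about 100% |

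**4. Effect of adjustment, proportional-odds simulation.** N = 160, with 1,500 runs per scenario (Monte Carlo SE at most √(0.25/1500) = 1.3 points). Assumed control grades 0 to V are 50/15/20/10/3/2% (SD 1.30, close to the protocol's 1.32). A normal prognostic score has an assumed SD on the log-odds scale.

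| Conditional OR | Score SD | Unadjusted | Adjusted | Gain (points) |
|---|---|---|---|---|
| 0.5 | 0.5 | 54.9% | 58.5% | 3.6 |
| 0.5 | 0.8 | 51.3% | 59.2% | 7.9 |
| 0.5 | 1.2 | 44.4% | 56.1% | 11.7 |
| 0.4 | 0.5 | 77.4% | 81.4% | 4.0 |
| 0.4 | 0.8 | 76.1% | 80.1% | 4.0 |
| 0.4 | 1.2 | 65.3% | 80.3% | 15.0 |

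In this control distribution, with no covariate effect, OR 0.5 lowers the mean grade by 0.41 and OR 0.4 by 0.51. A further simulation of 400 runs at OR 0.33 and score SD 0.5 gave 90% unadjusted and 91% adjusted, which is the low end of the range.

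**5. Where the gain comes from.** At OR 0.5 and score SD 0.8, the mean log odds ratio moves from −0.617 to −0.703 and its SE from 0.312 to 0.326. The ratio rises from 0.617/0.312 = 1.98 to 0.703/0.326 = 2.16. The SE goes up; the estimate moves further from zero.

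**6. Validity.** Under the null (3,000 runs), rejection rates were 4.1% to 5.7% across both models, within or close to simulation error around 5%.

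**7. Chance imbalance.** For a factor with 30% prevalence (assumption), the 95% range of the between-arm difference is ±1.96 × √(0.3 × 0.7 × 4/160) = ±14 percentage points.

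**8. Secondary outcomes.** Compared with an unpaired test at follow-up, baseline adjustment multiplies the variance by 1 − r². The correlation r is an assumption: r = 0.4 gives 0.84 (as if N were 1.19 times larger), r = 0.6 gives 0.64 (1.56 times) and r = 0.8 gives 0.36 (2.78 times).

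**The case against.** The strongest objection is that the article never calls the ordinal model unadjusted. It names no covariates, and a covariate list commonly sits in the statistical analysis plan, which is not shown. That stands: a reader might infer that the investigators have ruled out adjustment, and the text does not support this. What remains is that the section does mention covariates for the mixed models and not for this primary outcome.

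Second, the trial has ample power for its own target: 160 participants against the 67 needed, so adjustment adds less than 1 point at one grade. That also stands. However, under the assumed control distribution the mean grade is 1.07, so a fall of one grade would remove nearly all complications. The article's background cites reductions of about 50% as well as trials with no difference. Halving the mean is a shift of 0.535 grade, for which the formula in step 3 gives about 66% unadjusted, 71% at R² 0.10 and 76% at R² 0.20. Effects below one grade are therefore worth planning for.

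Third, a reader might infer that collected baselines are ignored for the secondary outcomes. They are not: the adjusted mixed model can cover every outcome measured repeatedly. The single-time-point tests fit those with no baseline, namely the Comprehensive Complication Index, length of stay, discharge destination and delirium. Only the ambiguity about which analysis governs survives.

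**Conclusion.** The point holds as a modest efficiency recommendation. As written, the ordinal model gives up under 1 point of power at the planned 1-grade difference and roughly 1 to 15 points at 0.4 to 0.6 grade or odds ratios of 0.4 to 0.5. The size rests on assumed prognostic strength (R² 0.05 to 0.30, or a score SD of 0.5 to 1.2) and an assumed grade distribution. The simulation also estimates a single covariate coefficient, so a model with several terms would gain slightly less.

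Two stronger readings are not supported. One is that the unadjusted analysis is biased or invalid because allocation is unstratified: the type I error holds, and an imbalance of up to 14 points is ordinary chance variation that the test already allows for. The other is that precision is lost in the ordinal model: adjustment widens the standard error of the log odds ratio slightly and gains power only.

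For secondary outcomes with a baseline, the fault is an unresolved duplication of analyses.

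**What to change.** In the section on statistical methods, or in the analysis plan before any unblinded look at outcomes:

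- Fit the ordinal model with treatment, site (with a rule for pooling small sites), indication (colorectal cancer or liver metastases, as recorded before randomisation), Charlson index and baseline 6MWT. Report the model without covariates as a sensitivity analysis.
- For chair stands, inspiratory pressure, the EORTC scales, the ADL-staircase and PASE, name the baseline-adjusted mixed-model contrast, or an ANCOVA, as the single decisive comparison at a stated time point.
- Keep the unpaired, chi-squared and Fisher tests for outcomes without a baseline: the Comprehensive Complication Index, length of stay, discharge destination and delirium.

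The cost is a few lines of text and no new data. The ordinal model gains at most six parameters (three for site, one each for the others, with Charlson index and 6MWT entered linearly). The adjusted odds ratio is conditional on the covariates and should be described that way.
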